## Abstract

**Background:**

Improving the functional outcome following total knee arthroplasty (TKA) by using different alignment techniques remains controversial. The surgical techniques and technologies used so far to obtain these alignments have all suffered from inaccuracies. The use of robotic technology to plan and execute the bony resection provides increased accuracy for these various alignment techniques and may determine which will deliver superior function. Functional alignment (FA) is a newer surgical technique that aims to position the prosthesis with respect to each patients’ specific bony anatomy whilst minimising disruption to the soft tissue envelope. This trial aims to compare the patient and surgical outcomes of FA to the current gold standard surgical technique, mechanical alignment (MA), under randomised and blinded conditions.

**Discussion:**

Currently, MA remains the gold standard in knee replacement due to proven outcomes and excellent long-term survivorship. There are many alternative alignment techniques in the literature, all with the goal of improving patient outcomes. This study is unique in that it leverages an advanced analytics tool to assist the surgeon in achieving balance. Both alignment techniques will be executed with high precision using the CT-based robotic arm-assisted surgery system which will minimise surgical variation. This trial design will help determine if FA delivers superior outcomes for patients.

**Trial registration:**

Australia and New Zealand Clinical Trials Registry (ANZCTR), ACTRN12620000009910. Registered on 9 January 2020. ClinicalTrials.gov, NCT04600583. Registered on 29 September 2020.

## Introduction

### Background and rationale {6a}

Total knee arthroplasty (TKA) is an established treatment for patients with symptomatic end-stage osteoarthritis. The aim of TKA is to provide pain relief and restore function; however, published literature identifies a consistent subset of patients who are not satisfied post-operatively [1–3]. Accuracy of limb alignment, implant position and soft tissue balance are important factors that influence the outcome of TKA [4–7]. It is theorised that modern prosthesis and surgical systems with high precision could assist the surgeon in optimising these factors to an individual patient’s anatomy, which may reduce the dissatisfaction rate following TKA.

Mechanical alignment (MA) has long been the gold standard in TKA and has shown excellent survivorship of 82.3% at 25 years, indicating that most knee replacements will outlast the patient’s lifetime [8]. This technique targets a neutral limb alignment through perpendicular bone resections relative to the mechanical axis of the femur and tibia [9]. It also aims for symmetrical and balanced gaps in flexion and extension, which may require surgical release of the soft tissues [6, 10, 11]. More recently, surgeons have utilised adjustments to bone cuts to achieve balance, such as minor adjustments to femoral rotation for flexion balancing, or leaving up to 3° residual varus in the tibial cut to minimise the need for soft tissue release [12]. Surgeons following these steps often refer to the technique as adjusted mechanical alignment (aMA). A recent publication by Macdessi et al. [13] showed that only 14.6% of arthritic patients have a neutral limb alignment and neutral joint line, as defined by a window of ± 3° and ± 2°, respectively. This indicates that most patients will require surgical adjustments to achieve a goal of MA or aMA, which may alter their native bony and soft tissue anatomy. Furthermore, surgical lengthening of ligaments is a challenging component of the procedure and can be highly variable [14, 15].

For these reasons, surgeons have investigated alternative alignment philosophies to achieve balance in TKA. Kinematic alignment (KA) aims to restore the patient’s native pre-arthritic knee anatomy through symmetrical bone resections relative to the femoral and tibial joint lines [16, 17]. It does not have prescribed alignment boundaries and suggests minimal adjustments to the soft tissue are required if the joint is resurfaced with the implant. However, multiple randomised control trials (RCT) have subsequently found minimal difference in patient outcomes when compared against traditional MA techniques [18]. Arguments for confounders can be made that studies on KA have used a variety of implant designs, surgical technologies with varying degrees of accuracy, and do not always report the corrections in bony morphology or soft tissue corrections [19].

Both MA and KA seek the same outcome: a reliable surgical technique and optimised patient outcome without compromising survivorship. Whilst MA relies on ligamentous adjustments to achieve balance and KA seeks to restore the native bony anatomy through controlled resections, neither considers both aspects together. More recently a technique called functional alignment (FA) was described, which aims to restore the patients native limb alignment and joint line obliquity by adjustments to the implant position based on individual patient bony anatomy and soft tissue balance [20]. The emergence of this technique has coincided with the increasing popularity of image-based robotic arm-assisted surgery, which provides high precision bone resections [21], intraoperative soft tissue laxity assessment allowing for pre-resection balancing [22] and insight into the native anatomy through a pre-operative CT scan [23]. Further, robotic systems that offer haptic control can preserve the soft tissues, particularly the posterior cruciate ligament [23], thereby assisting in the recreation of native kinematics. Whilst long-term data is currently lacking, early cohort studies on robotic arm-assisted TKA following FA principles show promising results [24–26].

There are no published prospective RCTs investigating robotic arm-assisted TKA with FA. Currently, there are two RCTs being conducted in Australia [27, 28] and one at University College London Hospital [29]. All three trials differ in their surgical alignment limits, balancing algorithm and use of assistive technology. The combined results of various trials may help determine the ideal surgical technique for different patient phenotypes [13].

### Objectives {7}

The primary objective of this study is to compare the Forgotten Joint Score (FJS) in MA TKA versus FA TKA at 2 years post-operatively. The FJS is a score that measures the restoration of ‘normal joint feeling’, and the hypothesis is that patients undergoing FA TKA will have a superior score.

The secondary objectives compare the following measures between each cohort:Other patient reported outcomes including: Oxford Knee Score (OKS), International Knee Society Score (IKSS), Knee Injury and Osteoarthritis Outcome Score (KOOS) and SatisfactionMeasures of pain throughout the care pathway using the visual analogue scale for pain (VAS Pain), Brief Pain Inventory (BPI) and Pain Sensitivity Questionnaire (PSQ)Post-operative rehabilitation measured through functional tests and range of motion in the operative jointEarly recovery data focusing on pain, medication and physiotherapy through recovery data collection formHealth-related quality of life assessed through EQ-5D-5LPatient experience assessed through the care pathway using the Net Promoter ScoreSurgical efficiency by comparing operative times, implant positions and soft tissue laxity measures using the robotic system, in conjunction with pre- and post-operative long leg weight bearing x-raysComplications assessed through adverse events and revision procedures

### Trial design {8}

This study is a prospective, singe-centre, single blinded, randomised controlled trial, where 240 patients will be allocated to robotic arm-assisted TKA following either MA (control group) or FA (intervention group). Participants will be randomly allocated in blocks of four following their eligibility assessment and provision of consent. The study seeks to assess if the interventional surgical technique is superior to the control, where superiority is defined as a patient reported outcome that meets the minimum clinically important difference (MCID) and patient acceptable symptom state (PASS) at 2 years.

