### Sample size {14}

This trial seeks to determine if robotic arm-assisted TKA following FA principles provides superior clinical outcomes to robotic arm-assisted TKA following MA principles. Ingelsrud et al. [41] reported that the minimal clinically important change in FJS for TKA patients was 14 points. As there is limited published literature on FA performed with robotic arm-assistance, the power calculations have assumed an effect size of 14, which represents a measure of superiority. A standard deviation of 26 is estimated using the Spearman correlation of 0.61 between the anchor score and change score from patients classified as ‘somewhat better’, which is also taken as a measure of superiority. Using a power of 80% (*β* = 0.2), significance level of 5% (*α* = 0.05) and accounting for 10% loss to follow-up yields a sample size of 120 participants per arm.

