### Statistical methods

#### Statistical methods for primary and secondary outcomes {20a}

The primary and secondary outcome data gathered from patients in each study group will be pooled and summarised. The mean, standard deviation and 95% confidence intervals will be calculated for each measure in each group. All outcome measures will be assessed on their distribution and homogeneity to confirm the appropriate statistical model. A mixed-effects linear model will be used to compare longitudinal outcomes between the FA TKA (intervention) to the MA TKA (control), with pre-operative measures as a covariate. Adjustments will be made for multiple testing over time. Pairwise comparisons will be examined using a paired *t*-test if normally distributed or non-parametric test for skewed distribution. Categorical data will be evaluated using frequency and percent distributions, with significance testing performed using Fisher exact test or chi-squared test. Statistical significance is defined as a *p*-value < 0.05. Clinical significance will be assessed against the MCID and the PASS as defined in Orr et al. [42].

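### Superiority is defined as a patient reported outcome meeting MCID and PASS, which is neither the powered FJS comparison nor the role that the analysis section gives MCID and PASS

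*Protocol article*

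**What the plan says.** Four parts of the protocol article bear on what counts as success.

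- **Trial design {8}:** "superiority is defined as a patient reported outcome that meets the minimum clinically important difference (MCID) and patient acceptable symptom state (PASS", at 2 years. It names no instrument and no threshold. It does not say whether the rule applies to a group mean, a between-arm difference or individual patients.
- **Objectives {7}:** the primary objective is to "compare the Forgotten Joint Score (FJS) in MA TKA versus FA TKA at 2 years post-operatively", and "the hypothesis is that patients undergoing FA TKA will have a superior score". The Abstract also names FJS at 2 years as the primary outcome.
- **Sample size {14}:** a cited study "reported that the minimal clinically important change in FJS for TKA patients was 14 points", and "the power calculations have assumed an effect size of 14, which represents a measure of superiority". The calculation uses SD 26, 80% power, 5% significance and 10% loss, and gives 120 per arm.
- **Statistical methods {20a}:** statistical significance is p < 0.05. Separately, "Clinical significance will be assessed against the MCID and the PASS", with both thresholds taken from a different cited study and no values given.

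Table 1 in Outcomes {12} schedules FJS at 6 weeks and at 6, 12 and 24 months, but not pre-operatively.

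**The concern.** The document holds two success rules. In one, MCID and PASS are the definition of superiority. In the other, superiority rests on a significance test of the FJS difference, and MCID and PASS help to interpret it. An SAP can add detail to a rule, but it should not have to choose between two rules in the protocol.

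The Trial design rule is also hard to apply to the primary endpoint. PASS is a threshold on a score, so a between-arm difference cannot meet it. The MCID, read at patient level, needs a change from baseline, and no baseline FJS is collected.

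Suppose the trial shows a clearly significant FJS difference of 10 to 12 points. The analysis section would support a claim of superiority, while the design section might deny it. The investigators and research team are not blinded, and results are to be analysed for dissemination at 6 months and 1 year, so the choice of rule could be made with data in view.

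**Working it through.** **Inputs.** From Sample size {14}: difference 14, SD 26, power 80%, alpha 5%, loss 10%, 120 per arm. Two assumptions are added. Alpha is two-sided, because sidedness is not stated. Allocation is 1:1, from the equal arms in Sample size {14} and the blocks of four in Trial design {8}; the Abstract's 4:1 ratio disagrees. Evaluable patients per arm: 120 × 0.9 = 108.

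**The plan's own figure.** n per arm = 2 × (1.960 + 0.842)² × 26² / 14² = 54.1, so 55 evaluable. Dividing by 0.9 gives 62 per arm. The stated 120 per arm is not reproduced. Unrounded, the total is 108.3 / 0.9 = 120.3, so 120 fits the total. That is a separate matter. Here it only means that the ordinary test has more power than the stated 80%. The stated 120 per arm is used below.

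**Standard error.** SE = 26 × √(2/108) = 3.54.

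**Reading A: ordinary two-sided test of the mean difference.** Power = Φ(δ/SE − 1.96).

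**Reading B: observed mean difference must be at least 14.** Probability = Φ((δ − 14)/SE). Any observed difference above 1.96 × 3.54 = 6.9 is already significant, so adding p < 0.05 changes nothing.

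| True difference δ | A: ordinary test | B: observed ≥ 14 |
|---|---|---|
| 14 | 97.7% | 50% |
| 12 | 92% | 29% |
| 10 | 81% | 13% |

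Under B, the 50% at δ = 14 does not depend on n, because the threshold equals the true value. An 80% chance needs δ = 14 + 0.842 × 3.54 = 17.0.

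**Reading B with another MCID.** The document gives no value for the MCID in Statistical methods {20a}. With assumed values and δ = 14, the chance is 87% for an MCID of 10, 71% for 12 and 29% for 16.

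**Reading C: B, and the FA arm mean must also reach PASS.** No PASS value is given, so the result is shown by the distance of the true FA mean from PASS, at δ = 14 and 108 per arm:

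- exactly at PASS: 37%
- 2.5 points above: 49%
- 2.5 points below: 15%

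The 50% of Reading B is the upper limit.

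**Reading D: proportion of patients above a score threshold, compared between arms.** Assume FJS is normal with SD 26 and shifted by 14. A control proportion p then becomes Φ(Φ⁻¹(p) + 14/26) in the FA arm. Power of the two-proportion comparison at 108 per arm:

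| Control | FA | Power |
|---|---|---|
| 20% | 38.1% | 84% |
| 40% | 61.2% | 88% |
| 60% | 78.6% | 85% |
| 80% | 91.6% | 69% |

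This reading can use PASS, which needs only the 24-month score. It cannot use a patient-level MCID for FJS change, because Table 1 has no pre-operative FJS.

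**The case against.** The strongest reply is that the document, read as a whole, is clear enough. FJS at 2 years is named as primary in the Abstract and Objectives {7}, and Sample size {14} ties the 14 points to superiority. Statistical methods {20a} already separates statistical from clinical significance. On this view the defect is one loose sentence in Trial design {8}. Exact thresholds and responder definitions commonly sit in a full protocol or SAP that is not shown. Requiring a clinically relevant observed effect is also a legitimate, stricter design choice.

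Much of this stands, and it rules out some stronger inferences:

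- **A true 14-point benefit would succeed only half the time.** A reader might infer this without condition. It holds only if the rule means an observed mean FJS difference of at least 14, and Trial design {8} contains no 14.
- **Any of the many instruments could be used to claim superiority.** The wording is loose, but the Abstract, Objectives {7} and Sample size {14} point to FJS and the other instruments are secondary.
- **The two cited sources give different MCIDs.** The document shows two citations but only one value, so a difference cannot be shown.
- **A responder endpoint would be hopelessly underpowered.** At the trial's stated size it has about 69% to 88% power. It is unplanned, but not hopeless.

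The reply does not remove the contradiction. The sentence in Trial design {8} is worded as a definition of superiority, and it differs from the test that is powered and described in the analysis section. Missing thresholds could be left to an SAP, but conflicting rules could not.

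**Conclusion.** The point holds as a contradiction in the decision rule. Trial design {8} defines superiority by MCID and PASS on an unnamed patient reported outcome. The rest of the article sets up a between-arm FJS test at p < 0.05, with MCID and PASS used for interpretation.

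For the same true 14-point difference, the chance of declaring superiority is:

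- about 98% under the ordinary test;
- 50% if the observed mean difference must reach 14, and less if the FA mean must also reach PASS;
- about 69% to 88% for a responder comparison.

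These figures rest on SD 26, 108 evaluable per arm, 1:1 allocation and a two-sided 5% level. The responder range also assumes normality and control proportions of 20% to 80%. The 50% figure is one conditional scenario, not a property of the trial. The firm conclusion is that the article does not settle which rule applies and that the readings differ widely.

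**What to change.** In Trial design {8}, replace the definition. Superiority is concluded if the intention-to-treat between-arm difference in mean FJS at 24 months favours FA, with a two-sided 95% CI excluding 0.

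Report that difference and its CI against one pre-stated MCID from one source. Report the proportion reaching PASS at 24 months as a secondary responder outcome, with a risk difference and CI. Both then serve clinical relevance, as Statistical methods {20a} already intends.

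The cost is protocol and SAP wording; no further patients or data are needed. The downside is that clinical relevance is interpreted alongside the test and no longer forms part of the success rule. If the sponsor prefers to keep MCID in the rule, the protocol must state the exact rule (instrument, threshold, group or patient level, and whether the estimate or the confidence limit must pass) and give its power.

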## Methods: participants, interventions and outcomes

### Study setting {9}

The study will be conducted in the Orthopaedic Department at North Shore Hospital, Auckland, New Zealand, which falls under the governance of the Waitemata District Health Board. All patients will have surgery, inpatient stays and follow-up at North Shore Hospital or the Elective Surgery Center, which presides within the hospital campus.

### Eligibility criteria {10}

The inclusion criteria are as follows:The patient is a male or non-pregnant female between the ages of 40 and 80 yearsThe patient requires a primary total knee replacement and is indicated for robotic-assisted surgeryPatient is deemed appropriate for a cruciate retaining knee replacementThe patient has a primary diagnosis of osteoarthritis (OA)The patient has intact collateral ligamentsThe patient is able to undergo CT scanning of the affected limbThe patient has signed the study specific, ethics-approved, informed consent ocumentThe patient is willing and able to comply with the specified pre-operative and post-operative clinical and radiographic evaluations

The exclusion criteria are as follows:The patient has a history of total, unicompartmental reconstruction or fusion of the affected jointPatient has had a previous osteotomy around the kneeThe patient is morbidly obese (BMI > 41)The patient has a deformity which will require the use of stems, wedges or augments in conjunction with the Triathlon Total Knee SystemThe patient has a varus/valgus deformity ≥ 15°The patient has a fixed flexion deformity ≥ 15°The patient has a neuromuscular or neurosensory deficiency, which would limit the ability to assess the performance of the deviceThe patient has a systemic or metabolic disorder leading to progressive bone deteriorationThe patient is immunologically suppressed or receiving steroids in excess of normal physiological requirementsPatient has a cognitive impairment, an intellectual disability or a mental illnessThe patient is unable to speak EnglishThe patient is pregnantThe patient has metal hardware present in the region of the hip, knee or ankle (as this is known to create geometrical distortion in the region of the implant)

All patients will be screened by the orthopaedic consultant surgeon and research coordinator based on the criteria. Patients that meet these criteria and express an interest in participating will be provided an ethics approved patient information sheet following initial consultation with their treating doctor. This sheet provides more detail about the study, potential risks and requirements for follow-up. The research coordinator will assist in scheduling their pre-operative visits if the patient decides to participate in the study. Pre-operative visits include the collection of consent, CT scan, x-rays and completion of patient reported outcomes.

### Who will take informed consent? {26a}

Informed consent will be obtained by either the orthopaedic consultant surgeon or the research coordinator, both of whom are trained in the study requirements and will be appropriately onboarded. Consent will be collected at the pre-operative radiology visit which is scheduled up to 6 months before surgery, but normally occurs within 4 weeks of admission. Māori cultural support is also available as per the New Zealand ethics guidelines.

### Additional consent provisions for collection and use of participant data and biological specimens {26b}

Biological specimens are not collected as part of the study protocol and collection of participant data is incorporated into the consent process listed in the “Who will take informed consent? {26a}” section.

### Interventions

#### Explanation for the choice of comparators {6b}

All participants will undergo robotic arm-assisted TKA to control for surgical induced variability with the technology. MA is defined as the standard surgical technique in TKA, but its standardised approach is hypothesised to be a contributing factor to poorer functional outcome in some patients. FA is an individualised technique in TKA that aims to improve functional outcomes, but this is yet to be proven in an RCT. The high precision of robotic arm-assisted TKA will assist the surgeon in achieving both of the allocated surgical techniques.

#### Intervention description {11a}

All participants will undergo a pre-operative supine CT scan of the lower limb which will be loaded onto the robotic arm-assisted system to assist with planning, soft tissue assessment, ligament balancing and bone resections. In particular, the native bone anatomy will guide the starting implant positions for both MA and FA. Femoral resection landmarks are referenced from the most prominent point of the distal femoral condyles and the most posterior point of the posterior femoral condyles, avoiding osteophytes. Similarly, tibial resection points are placed at the midpoint of each plateau, two-thirds posteriorly in the anteroposterior plane.

All surgeries will be performed using a midline skin incision and a medial parapatellar approach with the femoral and tibial arrays placed extra-articular using bicortical pins. The pre-operative CT scan will be matched to the computer model following a verification process which identifies bony anatomy intra-operatively. The software will identify the hip centre and ankle position to calculate limb alignment. The haptic window defined in the robotic arm-assisted system allows for preservation of a tibial bone island ensuring the posterior cruciate ligament is maintained. All patients will receive a fully cemented Triathlon cruciate retaining implant (Triathlon, Stryker, Kalamazoo, MI, USA) with patella resurfacing. The patella and tibial bearing surfaces will use highly crosslinked polyethylene (X3™, Stryker, Kalamazoo, MI, USA). All procedures will be planned for a 9 mm polyethylene insert allowing for 1 mm adjustments to maximise range of motion and avoid hyperextension or ligament laxity. Femoral and tibial sizing are optimised using the 3D information provided by the CT scan.

For participants randomised to MA, the implant positions will be planned perpendicular to the femoral and tibial mechanical axis and aim to restore a neutral limb alignment (± 1°). Femoral component rotation is set to the trans-epicondylar axis whilst the tibial component is aligned to Akagi’s line, which connects the medial border of the patellar tendon to the middle of the posterior cruciate ligament [30]. In the sagittal plane, the femoral component is flexed between 0 and 5° to optimise implant size and prevent notching. The posterior slope is set to 0–3°, and a combined flexion limit (tibial + femoral component flexion) of 10° will be applied. Prior to any bone cuts, a manual varus and valgus stress is applied to the joint at 10° and 90° of flexion to provide a virtual gap assessment of ligament tension in the medial and lateral compartment. If balance cannot be achieved, then soft tissue releases will be performed by the surgeon.

For participants randomised to FA, the implant pre-operative plans will position the implants with equal medial and lateral resections of 6.5 mm from the subchondral bone of the femoral condyles to replicate the patient’s native anatomy. If present, bone wear is compensated for by adjusting the resection depth by 1–3 mm. Femoral rotation is therefore matched to the posterior condylar axis, and the tibial component is rotated to Akagi’s line. The proximal tibial resections will be set to 7 mm from subchondral bone in both the medial and lateral compartment. In the sagittal plane, the implants are positioned to match the patient’s native flexion and posterior tibial slope. Virtual gap assessment is then performed at 10° and 90° of flexion. The surgeon will then adjust implant position to achieve balance following FA principles [20], within set boundaries imposed on both coronal plane alignment and ligament laxities. Femoral component alignment is limited between 6° of valgus and 3° of varus, whilst tibial component alignment is limited to 6° of varus to 3° of valgus in the coronal plane, with an overall limb alignment target between 6° of varus and 3° of valgus. Gap balance is defined as an equal medial–lateral extension gap and equal gaps in the medial compartment from extension to flexion. A flexion gap differential in the lateral compartment up to 6 mm is permitted, as this represents the native laxity in the lateral flexion compartment and has been associated with improved patient outcomes [31]. Further, the implant used in this study is a single radius design and achieving isometric tension of the medial collateral ligament is thought to achieve a more natural pivot. An analytics tool is used to generate all possible balancing solutions based on surgeon defined alignment boundaries and balancing tolerances. A weighted scoring system assists the surgeon to select the optimal component alignment solution. The use of this algorithm also reduces surgical variability between all surgeons. If balance cannot be achieved within these boundaries, then soft tissue releases will be performed by the surgeon.

Intra-operative data will be collected from the robotic arm-assisted system, whilst in-patient rehabilitation data and discharge notes will be collected on the clinical research forms. Participants in both groups will follow the same in-patient post-operative rehabilitation programs and discharge criteria is based on the ability of the patient to mobilise with weight bearing and achieve a range of motion > 90°.

